### SSI

3.2

The SSI is twofold. First, we will be intervening directly with long‐term care workers to support them to carry out three target behaviours: (1) assist residents with day‐to‐day hearing and vision device use, (2) use appropriate communication and (3) mute TV/radio at the bedside and during mealtimes when communicating. These behaviours are fully specified in Table 1. We will be carrying out a multifaceted intervention that addresses the key barriers and enablers identified in our exploratory Phase 1 research [32, 33, 34], as described in Table 2. Second, one or two staff at each participating site will be assigned a ‘sensory champion role’. Previous studies have shown that designating one or more staff members as ‘champions’ in long‐term care facilities and providing them with additional training and responsibilities can enhance their competence in managing related issues, improve the quality of care and positively impact the health outcomes of residents [35]. A subsequent study reported that designated ‘hearing champions’ were effective in supporting staff in relation to the maintenance of hearing aids and the use of communication strategies for residents with hearing impairment [36]. The sensory champion may be a registered nurse, care worker or therapy assistant, and will be employed in this capacity for 2−3 days per week for 3 months at each site. A description of the tasks completed by the sensory champion is outlined in Table 3.

**Table 1 hex70175-tbl-0001:** Full specification of staff behaviours targeted in the sensory support intervention.

Behaviour	Full specification
Assist residents with day‐to‐day hearing/vision device use	Each morning, check glasses are on and clean (glasses wearers) Each morning, check that hearing aids are on, inserted correctly and on correct ears and working (HA users) Each evening, check hearing aids and personal listening devices are removed, wiped clean and stored safely and batteries are conserved (on charge/battery door open) (HA/ALD users) Each week, check frames are well aligned and in good order (e.g., screws tight, nose pads intact, no corrosion of metal frames or fragmentation of plastic) (glasses wearers)
Use appropriate communication	Gain attention Speak face‐to‐face Speak clearer, nearer, slower Make text brighter, bigger, bolder

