Sensory support prompt Use of visual cues and reminders in strategic locations	Forgetfulness to enact sensory support behaviours.	Tailored to each centre, use a physical prompt (e.g., a poster placed on the back of the main door of the resident's room).

**Table 3 hex70175-tbl-0003:** Summary of sensory champion role.

Intervention component	Description	Duration
Understand hearing and vision function	Baseline data pertaining to hearing and vision function collected by the research team will be shared with the sensory champion. NB: if the intervention is shown to be effective, we will advocate for screening measures to be incorporated into routine care.	NA (incorporated into data collection)
Sensory needs analysis	The sensory champion will extract hearing and vision records from the resident's chart (if available), confirm they are up‐to‐date, and discuss their preferences regarding hearing and vision device use and communication strategies.	Approximately 60 min
Provide information about intervention pathways	Based on the sensory needs analysis, residents will be provided with information about potential intervention pathways (if required).	Approximately 30 min
Sensory support station and sensory support prompt discussion	Discussions with residents about their preference for a designated area to store and maintain all their sensory support devices and related items. Additionally, discuss whether they are agreeable to placing visual prompts to remind staff of sensory support‐related tasks.	Approximately 30 min
Environmental audit	Residents' rooms will be audited to ensure they are optimally set up for hearing and vision impairment.	Approximately 30 min
Device troubleshooting and repair	Aged care staff will be informed that they can contact the Sensory Champion should a resident's hearing/vision aids stop working. The Sensory Champion will try to troubleshoot the problem (based on their training) and arrange for repair if required.	As needed
Referral to hearing and vision specialists and GPs	If requested, the Sensory Champion will facilitate referral to appropriate hearing, vision or medical services (e.g., for ear wax management and supported administration of eye drops).	As needed

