To evaluate the cost‐effectiveness of the SS intervention compared to standard care (RQ5), we will report a within‐trial analysis, economic modelling and a budget impact analysis. The within‐trial analysis will include two components: (1) the health benefits associated with QoL outcomes for participants, as well as informal caregivers (RQ1), and (2) costs associated with intervention and healthcare resources using a micro‐costing study. We will estimate the intervention cost by recording the time spent by long‐term care workers on supporting residents' hearing and vision needs over 5 days, and extrapolate it over the relevant time horizon. Healthcare resource use will be measured at baseline and at a 3‐ and a 6‐month follow‐up using the Resource Utilisation in Dementia (RUD) Lite [72, 73], a standardised tool for collecting resource use data in dementia care. Since the tool was originally developed for community settings, only the section related to patient healthcare resource utilisation will be used to fit long‐term care settings. For informal caregivers, we will use the three sections of the RUD Lite concerning caregivers detailing primary caregiver description, time and work status.

Unit prices will be sourced from the corresponding Medicare Benefits Scheme items, Pharmaceutical Benefits Scheme items, the National Hospital Cost Data Collection [74] and other relevant sources.

We will estimate the lifetime cost‐effectiveness of the intervention using economic modelling (e.g., Markov modelling). We will conduct a literature review to inform the model structure and parameters not sourced from the intervention study. We will also report a budget impact analysis to determine the financial implications of implementing the SSI for the federal government. We will report the results of the cost‐effectiveness analyses according to the Consolidated Health Economic Evaluation Reporting Standards (CHEERS) checklist [75].

The economic evaluation outcome will be the incremental cost‐effectiveness ratio (ICER), which will determine whether the intervention is cost‐effective using Australia's implicit cost‐effectiveness threshold [76]. The ICER represents the incremental cost associated with a unit gain of health outcome of interest (e.g., a QALY) between two interventions.

The equation for the ICER is represented as:

$$\mathrm{ICER}=\frac{C_{1}-C_{0}}{E_{1}-E_{0}}$$
where *C*
_1_ and *C*

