_0_ are the costs associated with the long‐term care model and the usual care, respectively, while *E*
_1_ and *E*
_0_ are the effectiveness estimates (QALYs) of the of the long‐term care model and the usual care, respectively. The numerator and denominator for the ICER calculation will be estimated using generalised linear models accounting for data distribution and covariates. Sampling uncertainty will be handled by nonparametric bootstrap sampling. Bootstrap iterations will be plotted in the cost‐effectiveness plane and cost‐effectiveness acceptability curves.

For the economic model, uncertainty around the lifetime cost‐effectiveness results will be explored using deterministic and probabilistic sensitivity analysis.

For the budget impact analysis, we will report the cost to the federal government in Australian dollars. We will estimate this cost to the Australian healthcare system using projected utilisation estimates of SSI in Australia in the long‐term care setting over a relevant time horizon.

RQ6‐8: Descriptive statistics will be used to examine reach, adoption, implementation and acceptability. The qualitative interviews will be transcribed verbatim and analysed using mixed deductive‐inductive thematic analysis [77] to explore (1) the acceptability of the intervention to residents, long‐term care workers and informal caregivers, (2) the mechanisms through which staff behaviour change occurred and (3) the impact of contextual factors on implementation. Coding frameworks will be developed a priori based on the Theoretical Framework of Acceptability [69], the Capability, Opportunity, and Motivation Model of Behaviour (COM‐B) [30, 31] and the CICI framework [70]. After thoroughly reading interview transcripts, meaning units will be assigned to the most appropriate theoretical construct after which subthemes will be identified inductively using Braun and Clarke's methodology [78]. Rigour will be enhanced through regular peer consensus meetings between two coders performing independent double coding and other members of the research team. Qualitative results will be reported in line with the consolidated criteria for reporting qualitative research (COREQ).

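### The stated intervention-cost method, 5 days of care-worker time extrapolated forward, does not fit an intervention with a 3-month champion post, training sessions and equipment

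*Protocol article*

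**What the plan says.** In the Data Analysis Plan (3.6), the within-trial analysis is to include "costs associated with intervention and healthcare resources using a micro‐costing study". The next sentence gives the method for the intervention part: "recording the time spent by long‐term care workers on supporting residents' hearing and vision needs over 5 days, and extrapolate it". The length of the horizon for this extrapolation is not given, nor when the 5 days fall. The ICER numerator is C1 − C0, which "are the costs associated with the long‐term care model and the usual care, respectively".

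Section 3.2 describes what has to be costed. On the champion role, "one or two staff at each participating site will be assigned" to it. The champion may be a registered nurse, a care worker or a therapy assistant, and "will be employed in this capacity for 2−3 days per week for 3 months at each site". Table 2 adds 60-minute training sessions held on several days, sensory stations with cleaning and maintenance kits, and visual prompts. Table 3 gives approximate durations for four champion tasks. For hearing and vision function its duration entry is "NA (incorporated into data collection", because the research team collects those data. The same row says the authors would advocate routine screening if the intervention is shown to be effective.

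**The concern.** The costing rule measures one kind of input, care-worker time, at one rate. The intervention has at least three other kinds: a temporary salaried post, training hours and goods. A time record of resident support cannot pick up goods at all, and training is not time spent supporting residents. The champion's hours enter only by coincidence of job title and timing.

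Extrapolating a single 5-day rate raises a second problem. A start-up cost that lasts 3 months is missed if the 5 days lie outside that period. If they lie inside it, the cost is continued beyond the period in which it was incurred.

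A third problem concerns usual care. The design is pre-post without a concurrent control, so the usual-care level of support time must come from baseline or from an outside source, and the article names neither for this quantity.

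The intervention cost feeds the ICER and is needed for the lifetime model and the federal budget impact. Omitting start-up items lowers C1 and favours the intervention. Repeating a temporary cost, or charging pre-existing support to the intervention, does the opposite.

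**Working it through.** The article states no cost, ICER or staff-hour total, so there is no figure to reproduce. The check sets the components against the rule and then sizes what falls outside it.

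**Which components the 5-day record can reach**

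- Daily device and communication support by care workers: yes.
- Champion: only if the champion is a care worker (the Sample section defines these as staff giving daily personal care) and the 5 days fall within the 3 months.
- Training, trainer and attendees: no.
- Station kits, labels, prompts: no, as they are not time.
- Screening: research activity within the trial, so not a within-trial intervention cost.

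**Champion time.** Inputs from 3.2: 2 to 3 days a week, 3 months (13 weeks), one or two champions per site. Assumptions: a 7.6-hour day, and all 87 residents at one site.

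- Days per champion: 2 × 13 = 26 to 3 × 13 = 39.
- Hours, one champion: 26 × 7.6 = 198 to 39 × 7.6 = 296.
- Hours, two champions: 395 to 593.
- Per resident: 198 / 87 = 2.3 to 593 / 87 = 6.8 hours.

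**Cross-check with Table 3.** The timed tasks total 60 + 30 + 30 + 30 = 150 minutes per resident, and 150 × 87 / 60 = 217.5 hours. This lies inside the one-champion range. These hours are work done within the post and are not additional to it.

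**Training.** If all 40 workers attend one 60-minute session: 40 hours, trainer time excluded.

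**Share of intervention hours (illustration).** The article gives no care-worker support time, so assume 2 to 10 minutes per resident per day over 91 to 182 days.

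- Care-worker hours: 2 × 87 × 91 / 60 = 263.9 to 10 × 87 × 182 / 60 = 2,639.
- Champion plus training: 197.6 + 40 = 237.6 to 592.8 + 40 = 632.8 hours.
- Lowest share: 237.6 / (237.6 + 2,639) = 8%.
- Highest share: 632.8 / (632.8 + 263.9) = 71%.
- At 5 minutes a day: 237.6 / (237.6 + 1,319.5) = 15% to 632.8 / (632.8 + 659.75) = 49%.

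A 7.5-hour day gives 8% to 70% for the full range.

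**Carrying the champion forward.** If the 5 days do capture champion time and the rate is extended over H weeks, champion time is multiplied by H / 13: 2 times at 26 weeks, 4 times at 52 weeks. Both values of H are assumptions.

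**Baseline support time.** Candidate sources for the usual-care side:

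- Field notes (3.5.1), at baseline and post-intervention: total duration of care from entering to leaving the room, not hearing and vision support.
- Task lists (3.5.2), at baseline and post-intervention: completion of tasks, not time.
- RUD Lite (3.6), at baseline, 3 and 6 months: residents' healthcare use, not staff support time.
- The 5-day record (3.6): the right quantity, but no baseline occasion is stated.

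If a share b of post-intervention support time already existed at baseline and were not subtracted, the increment would be overstated by 1 / (1 − b): 1.33, 2 and 4 times for assumed shares of 25%, 50% and 75%.

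**The case against.** The strongest reply is that one sentence is being read as a complete inventory. The sentence before it promises micro-costing of the intervention, unit prices may come from other relevant sources, reporting follows CHEERS, and the process evaluation records champion task completion and training attendance. Nothing says that champion or training costs will be excluded, and an article may leave a full cost list to a fuller plan. This stands against the inference that the ICER numerator is wrong: the documents do not show that. It does not remove the point, because the sentence that says how intervention cost will be estimated names only care-worker time, and a time record extrapolated at one rate is the wrong form for temporary or material inputs.

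A reader might also infer that costs will not be net of baseline. The article does not support this, since C1 − C0 against usual care is explicit. What stands is that the support-time part of C0 has no stated source.

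Nor can the champion be called the largest cost item. No unit costs or care-worker times are given, and the illustrated share of hours runs from minor to dominant.

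Finally, leaving screening out of the within-trial cost is defensible. It becomes a cost only if screening enters routine care, and so belongs in the lifetime model and budget impact.

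**Conclusion.** The point holds as a fault in the stated costing rule. Followed literally, the rule omits training and kits, catches the champion post only by coincidence, and treats a 3-month cost as a continuing rate. Netting of support time is unclear rather than absent.

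Only the 26 to 39 days per champion per site and the 217.5 hours of timed tasks for 87 residents come directly from the article's figures, taking 3 months as 13 weeks. The 198 to 593 hours rest on a 7.6-hour day, and the per-resident figures also on one site. The 40 training hours rest on full attendance, and the shares and multipliers on the ranges stated above. No corrected ICER can be calculated. The net direction is not determined: omitted items favour the intervention, while repeated or un-netted items count against it. The issue concerns the economic question, a secondary one, but should be settled before data collection because champion and training hours are hard to reconstruct afterwards.

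**What to change.** Define intervention cost in 3.6 as the sum of two parts.

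- **One-off:** champion employment for the 3 months, trainer and attendee hours, and station kits. Cost the champion from payroll or from logged task hours, not both.
- **Recurrent:** post-intervention minus baseline care-worker time on hearing and vision support, with the 5-day record taken in the same way at both periods. State when each record is taken.

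Extrapolate only the recurrent increment. Enter any champion or training refresh, and screening at routine-care staff cost, as explicit inputs to the lifetime model and budget impact analysis only.

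The cost is more than wording. The champion log is planned for contextual influences and would need an hours field, and a matching 5-day baseline record may be new data collection. Training attendance is already to be recorded. The ICER may turn out less favourable.

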## Research Questions

2

This study uses prospective pre−post‐intervention trial design. The primary research question (RQ) is:

What is the impact of the SSI on the quality of life of residents and their informal caregivers (i.e., unpaid care provided by family, close relatives and friends) [37]? This RQ will be explored through standardised questionnaires (e.g., the Health Utilities Index 3 [HUI‐3] [38] and the Quality of Life‐Aged Care Consumers questionnaire [QOL‐ACC] [39], described below).

Secondary research questions include:

What is the impact of the SSI on care workers' (formal caregivers of people living in long‐term care) use of sensory support behaviours? This RQ will be explored through direct observation and questionnaires.

What is the impact of the SSI on residents' use of hearing and vision devices, quality of resident‐staff communication, well‐being, sensory function and behaviour? This RQ will be explored through direct observation, self (or proxy) report questionnaires and professional caregiver report.

What is the impact of the SSI on informal caregivers' well‐being and relationship with residents? This RQ will be explored through questionnaires.

What is the cost‐effectiveness of the SSI compared to standard care? This RQ will be explored through direct observation and questionnaires.

A simultaneous process evaluation is also planned to address the following research questions:

To what extent was the SSI considered acceptable to care workers, residents and informal caregivers and implemented as intended? Acceptability will be explored through a post‐intervention survey and individual structured qualitative interviews, and implementation will be evaluated based on inspection of daily task sheets that record the daily duties of care workers.

What were the mechanisms through which the SSI achieved/did not achieve impact? This RQ will be explored using individual, semi‐structured, in‐depth interviews.

How did contextual factors impact the implementation of the SSI? This RQ will be explored by analysing the written log completed by the sensory champion, supplemented by a structured qualitative interview.

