### Sample

3.1

Participants will include three groups: (1) people living in long‐term care, (2) informal caregivers of people living in long‐term care and (3) long‐term care workers. All participants will be recruited from a single long‐term care setting in Perth, Western Australia, who we partnered with to develop the intervention. All people living at the participating long‐term care setting over the age of 65 will be eligible to take part, irrespective of their sensory or cognitive functioning. Informal caregivers will be eligible to participate if they are aged 18 years or older and are a family member or friend of a resident participating in this study. Informal caregivers will be excluded if they are not in regular contact with the resident. Long‐term care workers will be eligible to participate if they currently work in the participating long‐term care setting and are involved in the provision of daily personal care to residents participating in this study.

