#### Primary Outcome

3.5.1

Residents' quality of life will be measured using the interviewer‐administered versions of the HUI‐3 40Q [38] questionnaire with 1‐week recall, and the Quality of Life‐Aged Care Consumers (QOL‐ACC) [39] instrument. The HUI‐3 captures the sensory quality of life attributes and therefore will be more sensitive to the effect of the intervention. The interviewer‐administered version of the HUI‐3 was chosen as some participants will likely have mild cognitive impairment or dementia and therefore many may be unable to complete a self‐report measure. The QOL‐ACC will also be used to capture the quality of life as the HUI‐3 has shown inconsistencies in people with dementia. The QOL‐ACC has been validated both for people with dementia and people living in long‐term care [48] and is routinely collected by the Australian Government for long‐term care residents. We will measure QoL using both self‐assessed and proxy‐assessed versions of both HUI‐3 and QOL‐ACC to ensure completeness, where proxy‐assessment will be completed by the informal caregivers or long‐term care workers where an informal caregiver is not available. QOL‐ACC and HUI‐3 responses will be used to estimate utilities with an Australian algorithm [49, 50]. Utilities will be used to estimate quality‐adjusted life years (QALYs), which combine the utility of a health state with the time spent on that health state. QALYs will be used as the benefit measure in the cost‐effectiveness analyses. To capture the impact of the SSI on the duration of daily care delivery, a research assistant will use field notes to record the duration of daily care delivery based on direct observation of care workers entering and leaving the resident's room during baseline and post‐intervention periods.

Informal caregivers' quality of life will be evaluated using the 5‐item EQ‐5D‐5L [51], which evaluates five dimensions, including mobility, self‐care, usual activities, pain/discomfort and anxiety/depression. Higher scores reflect poorer quality of life. Utilities will be estimated using an Australian algorithm [51, 52].

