### Data Analysis Plan

3.6

We will apply methods (e.g., Bonferroni correction) to control for family‐wise error rates for each research question. Data analysis will be conducted with SPSS [71].

Two generalised linear models will be applied to evaluate the impact of the SSI on the quality of life of residents and their informal caregivers. For both, the dependent variables will be the individual domains of quality of life (resident or informal caregiver) and the independent variable will be time. Potential covariates will include demographic variables, (resident) health status, (resident) cognitive and sensory functioning, (resident) use of hearing and vision devices and use of long‐term care workers' sensory support behaviours.

Paired *t*‐tests (or other repeated measures test) will be used to examine pre‐/post differences in long‐term care workers' use of sensory support behaviours.

A series of generalised linear models will be used to evaluate the impact of the SSI on residents' use of hearing/vision devices, quality of patient‐provider communication, well‐being, sensory function and behaviour. For each model, the independent variable will be time and potential covariates will include demographic variables, health status, cognitive and sensory functioning and use of long‐term care workers' sensory support behaviours.

Two generalised linear models will be applied to evaluate the impact of the SSI on informal caregivers' well‐being and relationship with the resident. For each model, the independent variable will be time. Potential covariates will include demographic variables, resident health status, resident cognitive and sensory functioning and use of long‐term care workers' sensory support behaviours. The nested structure of the data will be taken into consideration in the modelling.

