## Discussion

5

This paper has described a protocol for the evaluation of an SSI that aims to improve hearing and vision outcomes for older people living in long‐term care by supporting the practice of long‐term care workers and improving long‐term care environments. This protocol entails a prospective pre−post‐intervention trial conducted within a long‐term care setting incorporating pre‐intervention assessments (baseline) and at 3 and 6 months post‐intervention. Concurrently, a process evaluation will be conducted during the trial to assess implementation, mechanisms of impact and contextual factors influencing the intervention's effectiveness.

The protocol was developed by an interdisciplinary team with expertise in co‐designing complex intervention, implementation science, long‐term care, behaviour change, health economics, health professionals, hearing and vision care and dementia. This diversity of expertise ensures that multiple perspectives are considered so that the evaluation will provide both information about the benefits of the SSI and the challenges and opportunities for implementation. The evaluation of the multidisciplinary SSI is aligned with the Medical Research Council guidance for process evaluation of complex interventions [79]. The use of both qualitative and qualitative methodology facilitates insights into the benefits of the intervention and contextual factors that may not be captured by quantitative measures alone. Evidence about the cost‐effectiveness and acceptability of the intervention will inform large‐scale implementation to improve the quality of care provided to older Australians and optimise health outcomes.

Limitations of this study include involving a single provider long‐term care setting in one country (Australia), which may limit the generalisability of the results. However, outcomes from this study would be relevant for any countries with similar models of aged care. The sample size is relatively small; however, the estimated number of participants should be parsimonious but at the same time sufficient to detect change in effect with precision.

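### The within-trial ICER is defined against usual care, but nobody is followed under usual care after baseline, so C0 and E0 rest on an unstated assumption and the result is a before-after contrast

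*Protocol article*

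**What the plan says.** RQ5 in section 2 of the protocol article asks: "What is the cost‐effectiveness of the SSI compared to standard care". Section 3.6 describes the ICER as a contrast between two interventions and defines its terms under the equation, where C0 and E0 belong to usual care ("care model and the usual care, respectively, while"). It then says: "The numerator and denominator for the ICER calculation will be estimated using generalised linear models accounting for data distribution and covariates". Sampling uncertainty is to be handled by nonparametric bootstrap, shown on the cost-effectiveness plane and in acceptability curves. The ICER is to decide whether the SSI is cost-effective against an Australian threshold.

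The design is pre-post. The Discussion describes "pre‐intervention assessments (baseline) and at 3 and 6 months post‐intervention". Section 3.1 says "All participants will be recruited from a single long‐term care setting in Perth, Western Australia", and "Participants will include three groups: (1) people living in long‐term care", the other two being informal caregivers and care workers. These are types of participant, not treatment arms. For the quality-of-life models that answer RQ1, section 3.6 names the outcomes, "and the independent variable will be time".

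A literature review is planned in section 3.6, but for the structure of the lifetime economic model and for the parameters that the study does not supply. The limitations in the Discussion are the single provider in one country and the small sample.

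**The concern.** QALYs and costs build up over time. E0 and C0 are what the same residents would have accrued over the follow-up period under usual care. One baseline assessment gives a starting level, not an accrued amount. To turn it into E0 and C0, something must be assumed about how utility and resource use would have moved without the SSI. The article names a usual-care comparator and an estimator, but no usual-care data after baseline and no assumption in their place.

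Followed as written, the plan would report a before-after contrast as cost-effectiveness against standard care. The size of that ICER, and even its sign, depends on the missing assumption, and a reader of the acceptability curves would not see this. The Discussion expects the cost-effectiveness evidence to inform large-scale implementation. The RQ1 models have the same feature: the time coefficient mixes any SSI effect with whatever else changes over 6 months.

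**Working it through.** **1. Is there a comparator anywhere in the design?** The sample size in section 3.3 settles this. Inputs: d = 0.3, correlation 0.6, attrition 20%, power 80%, two-sided 5%.
- Paired effect size: dz = 0.3 / √(2(1 − 0.6)) = 0.3354.
- Completers, normal approximation: n = ((1.960 + 0.842) / 0.3354)² = 69.8.
- Recruited: 69.8 / (1 − 0.20) = 87.2, against the stated 87.

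The stated figure is reproduced as a one-group before-after calculation. (With the noncentral t, n = 72; 72 / 0.8 = 90, while 72 × 1.2 = 86.4, which rounds up to 87. Either way it is one group.) Sections 3.2 and 3.5.3 speak of each participating site, but no untreated site and no staggered start is described.

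**2. Can a model on these data separate the SSI from time?** Take an intercept, indicators for month 3 and month 6, and an indicator for SSI exposure (0 at baseline, 1 afterwards). The SSI column equals the sum of the two month columns, so the matrix has rank 3 of 4. With a concurrent usual-care group, the model with group, time and their interaction has full rank, 6 of 6. Covariates do not resolve this in the one-group design without further assumptions, and the bootstrap resamples the same one-group data.

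**3. What does the missing assumption do to the ICER?** All inputs here are assumed; the documents give none. Suppose baseline is carried forward as usual care. Let u be the true utility gain, reached linearly at 6 months, and δ the change that would have occurred without the SSI, also linear. Then:
- True QALY gain = 0.5 years × 0.5 × u = 0.25u.
- Before-after QALY gain = 0.25(u + δ).

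With u = 0.05 and incremental cost held fixed:

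| δ over 6 months | Before-after QALY gain | ICER relative to the true one |
|---|---|---|
| 0 | 0.0125 | 1 |
| −0.025 | 0.00625 | doubled |
| −0.05 | 0 | undefined |
| +0.05 | 0.025 | halved |

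A second illustration shows the sign. Assume a gain of 0.03 at both 3 and 6 months and an incremental cost of AUD 500. The true QALY gain is 0.25 × 0.015 + 0.25 × 0.03 = 0.01125, and the ICER is 500 / 0.01125 = 44,444. Adding 0.25δ for δ = +0.03, −0.03 and −0.06 gives 0.01875, 0.00375 and −0.00375 QALY, so ICERs of 26,667, 133,333 and −133,333. A drift in resource use would shift the numerator in the same way.

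**4. What does it do to RQ1?** Approximate the time contrast by a paired t-test with 70 completers (87 × 0.8 = 69.6) and correlation 0.6, without covariates or multiplicity correction. The noncentrality is (net change in SD / √0.8) × √70.
- No true SSI effect, drift of 0.1, 0.2 or 0.3 SD in either direction: significant with probability 15%, 45% or 79%.
- True effect 0.3 SD, decline of 0.1, 0.2 or 0.3 SD: probability of significance falls from 79% to 45%, 15% or 5%.

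**The case against.** The strongest reply is that a pre-post design is legitimate and openly declared in the Abstract, section 2 and the Discussion, and that a time term is its ordinary model. This stands: the design is not an error. The inconsistency lies in attaching a usual-care comparator to it. For RQ1 the point concerns how the coefficient is described, not the model.

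A second reply is that a journal article condenses, and a full health-economic plan may say where C0 and E0 come from. In part this stands. The article does not say that baseline will be carried forward, nor that time is the exposure in the ICER models; a reader might infer both, but neither is stated. Still, it fixes the comparator and the estimator, and no data collection that it describes provides usual-care follow-up.

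Several stronger readings are tempting and not supported:
- That the plan ignores other causes of change. Section 3.6 lists potential covariates, and section 3.5.3 plans enquiry into mechanisms and context, including lockdowns and workforce issues. These do not identify the SSI effect, but they are there.
- That regression to the mean is a main source of bias. Section 3.1 admits residents over 65 whatever their sensory or cognitive function, so nobody is selected for a low score.
- That the within-trial ICER drives the budget impact analysis. Section 3.6 bases that analysis on cost and projected utilisation.
- That the lifetime model fails equally. Its usual-care inputs may come from the literature review, and it has its own sensitivity analyses.
- That a pre-baseline trend is readily available. Section 3.5.1 says that the QOL-ACC "is routinely collected by the Australian Government for" long-term care residents. It does not say that repeated individual scores can be retrieved, and no earlier series of HUI-3, EQ-5D-5L or RUD Lite data is described.

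**Conclusion.** The point holds for the within-trial economic evaluation and, as a matter of interpretation, for RQ1. The article promises a comparison with usual care that its single-group design cannot supply without an assumption about what would have happened without the SSI. That assumption is unstated, the planned data cannot test it, and neither covariate adjustment nor bootstrapping replaces it. This is a contradiction within the document, because comparator and design are both fixed there.

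The size cannot be derived from the documents. Under the assumed gain of 0.05, a modest background decline doubles the ICER and a decline as large as the gain removes it. These figures show sensitivity, not expected bias. Decline would work against the SSI and improvement in its favour; the documents give no figure for either.

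**What to change.** - In section 3.6, state the counterfactual that defines C0 and E0 over follow-up, for example baseline carried forward, and say that it is an assumption.
- Report the within-trial ICER and acceptability curves under flat, declining and improving usual-care scenarios, for utility and for cost.
- Label the within-trial result and the RQ1 estimates as before-after change, not as SSI versus usual care.
- In the Discussion, list the lack of a comparator among the limitations.
- Optionally, if repeated pre-baseline QOL-ACC values prove retrievable from routine records, use their trend as one further scenario. It would itself be an untested projection and would serve utility only, not cost.

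The first four changes need no new participants and no new data: they are wording plus scenario analyses. The price is a wider and probably less favourable cost-effectiveness statement.
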